**Two-sided 95% Confidence Intervals for Various SAE Rates**

| Sample Size | 0 events | 1 event | 2 events | 5 events | 10 events |
| --- | --- | --- | --- | --- | --- |
| N=100 | (0, 3.5%) | (0, 4.9%) | (0.4%, 6.6%) | (2%, 11%) | (4.9%, 17.1%) |
| N=200 | (0, 1.7%) | (0, 2.5%) | (0.2%, 3.5%) | (1%, 5.4%) | (2.6%, 8.7%) |

Power is calculated based on the exact test (or likelihood ratio test).  The type 1 error is assumed to be 0.05.  The following table shows the power to detect the difference with various SAE rates in the treatment group given SAE rate in placebo group equals 0.01.

**Power Calculation**

| SAE Rates in Treatment Group  (n=200) | Power |
| --- | --- |
| 0.03 | 17% |
| 0.04 | 36% |
| 0.05 | 56% |
| 0.06 | 73% |
| 0.07 | 85% |

## Methods of Analysis

Analysis Populations

Intent‑to‑Treat (ITT) Population

This population will include all participants who are randomized into the study and receive at least one dose of study medication. The exclusion of participants who do not receive study drug is justified by the fact that the decision to not initiate study medication is made with no knowledge of the randomized treatment. Participants with major eligibility violations that are identifiable based on pre-randomization characteristics will be excluded. Participants who receive study medication other than that intended will be analyzed according to the group to which they were randomized.

Analysis of the Conduct of the Study

This population will include all screened participants. Specifically, summaries of the following endpoints will be generated: participant screening, eligibility, participant enrollment, participant disposition and reasons for discontinuation, participant medication compliance, participant compliance with study visits, and protocol violations/deviations. Simple descriptive statistics, including percentages, means, and quartiles will be used to summarize the distribution of these endpoints. In addition, the above analyses will be carried out by clinical site to identify any potential site-specific issues. Participants’ disposition will be tabulated as screened but never enrolled, enrolled but never initiated study product, on-study and continuing with study product, discontinued from study product but continuing follow-up for HIV infection or off-study and not continuing follow-up.

*Types of Outcomes and Statistical Analyses*

The outcomes of interest and their respective analyses can be classified by the following factors:

Type of outcome and number of responses per individual:

A) Time until first occurrence of some specified event –

One response per individual – Cox survival regression

B) Yes/no outcome;

One response – Logistic regression

Multiple responses – Longitudinal binary regression

C) Continuous outcome

In general, counts (e.g. number of partners) will be treated as Poisson distributed

outcomes while laboratory values or transformations of those values (e.g. creatinine level,

log (creatinine level) will be treated as normally distributed outcomes.

One response – Poisson, linear regression

Multiple responses – Longitudinal Poisson, linear regression

All statistical analyses will be conducted using SAS© version 8.2 using PROC PHREG (survival analyses) and PROC GENMOD (logistic, Poisson, linear regressions for single or multiple responses). The analyses with multiple responses per individual will be treated as longitudinal regression models that will take into account that the responses tend to be correlated within individuals.

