## Randomization

Participants will be randomly assigned to one of the four arms: immediate study product receipt (TDF or placebo) or delayed study product receipt (TDF or placebo) in a 1:1:1:1 ratio. A CDC statistician will develop the allocation sequence using a permuted blocks randomization scheme. In a block of 8 study numbers, 2 assignments will be to immediate TDF, 2 to immediate placebo, 2 to delayed TDF, and 2 to delayed placebo. Randomization codes will be provided to Gilead Sciences, Inc., and study bottles will be labeled and filled with TDF or placebo using these codes and shipped to the appropriate site. Participants will be randomized to a group only after they have consented to participate and they have met the eligibility requirements for the study. Randomization will be stratified by study site. The list of treatment assignments and the assignment codes will be known only to the statistician and designated individual at Gilead Sciences, Inc., and only CDC will have access to the list of treatment assignments should the need for this information arise.

Group assignments will be concealed in sequentially numbered, sealed envelopes that will be distributed to each site by CDC and maintained in a secure location. After a participant has been properly enrolled in the study, a designated study staff member will obtain the next randomization envelope in sequence and be provided the information indicating the participant’s assignment to a delayed or immediate arm and the randomization number (bottle identification number) assigned.

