### Study Product Handling and Packaging

TDF or placebo tablets will be packaged at the Gilead manufacturing facility in white high-density polyethylene (HDPE) bottles. For the immediate arms, bottles will be packaged in kits of 7 bottles per participant. For the delayed arms, bottles will be packaged in 2 kits of 7 and one kit of 4 per participant. Each bottle will contain 30 tablets and a single silica gel canister to protect the product from humidity and fiber packing during handling and shipping. Study product should be stored before dispensing to participants at 25°C; excursions permitted to 15-30°C. Each bottle will be labeled with an identification number, the protocol number, administration instructions, expiration date, lot number, and sponsor address. Additional information will be included according to the protocol requirements and local law.

At the study sites, a designated staff person will transfer study product into another white HDPE fitted with a Medication Event Monitoring System (MEMS®) cap (52). Each bottle with the MEMS cap will be labeled with an identification number, the protocol number, administration instructions, expiration date, lot number, and sponsor address. Study product will be dispensed at enrollment, months 1 and 3 and then every 3 months thereafter for participants randomized to the immediate treatment arms. Participants randomized the delayed treatment arms will receive study product at 9, 10 and 12 months and then every 3 months thereafter. Participants will be instructed to return unused study product at each study visit. The investigator will be responsible for maintaining accurate records for all study bottles dispensed and returned. The inventory must be available for inspection by the study monitor. Study product supplies, including partially used or empty bottles and the dispensing logs, must be accounted for by the study monitor prior to destruction or return.

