## Enrollment Visit

HIV-1 negative persons who meet all of the inclusion criteria and none of the exclusion criteria at screening will be scheduled for an enrollment visit within 45 days of screening. The screening and enrollment visits may be spread over 2-3 visits. Study product must be initiated within 24 hours after the enrollment visit for participants randomized to one of the immediate treatment arms.

The following procedures and evaluations are to be performed at the enrollment visit:

*Epidemiologic/behavioral risk assessment*

Study staff will instruct participants on how to complete a 30 minute audio-computer administered self-interview (ACASI). This interview will collect risk behavior, adherence, and other behavioral data at enrollment and designated intervals throughout the study.

Clinical assessment:

- Enrollment form
- Baseline Medical History Form
- Concomitant Medication Form
- Complete Physical Examination

*Laboratory assessment:*

HIV-1 whole blood rapid EIA.

- Chemistry profile
- Hematology profile
- Urinalysis
- Urine for *Neisseria gonorrhoeae* (GC) and Chlamydia trachomatis (CT) testing
- Blood sample for storage

HIV risk reduction counseling

- Standardized HIV risk-reduction counseling by trained staff including study-specific issues:
  - the nature of the study (safety)
  - the unknown level of protection from the product
  - the possible assignment to placebo
  - the importance of avoiding HIV risk behaviors
  - symptoms that may be associated with acute HIV infection

Upon completion of enrollment assessments the investigator should dispense study products to those participants randomized to an immediate treatment arm based on the number assigned in the allocation sequence.

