# STATISTICAL CONSIDERATIONS

## Study Design and Analysis Plan Overview

This is a phase II randomized double-blinded placebo-controlled trial to assess the clinical and behavioral safety of daily oral use of TDF among MSM. Four hundred MSM at risk of HIV-1 infection will be recruited from two sites, randomized 1:1:1:1 to one of four treatment arms, and followed for 24 months. Two treatment arms will receive study product (TDF or placebo) for the entire 24 months (the immediate treatment arms) and the other two treatment arms will receive no study product for the initial 9 months and then receive either TDF or placebo for the remaining 15 months. The data analysis will compare clinical and behavioral safety data between the study arms. The analysis will employ the intent-to-treat principle whereby all data from enrolled participants will be analyzed according to the initial randomization assignment regardless of how many doses they received.

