## Safety Analyses for Behavioral Outcomes

Data will be collected on HIV risk behaviors at enrollment and 3-month intervals throughout the study to assess the behavioral safety of study product use. The main behavioral safety analysis will compare the overall level of selected behaviors in the immediate and delayed treatment arms over the first nine months of the study. Statistical analyses for dichotomous (yes/no) responses will account for the within-individual correlation using longitudinal binary regression models. The study will have good power (>80%) to detect differences in the probability of a yes response between the groups of 12% or more assuming that the probability of a yes response in the delayed group is 28% or greater. All analyses will account for within-individual correlation using longitudinal models for continuous variables (e.g. Poisson outcomes). Subsequent analyses will examine whether there is a trend in the difference of a yes response between the two groups over time and trends in the probability of a yes-response within both the TDF and placebo groups while on study product. This last analysis will also be examined in relation to an individual’s perception that they have been randomized to a TDF group.

In all analyses, study drop-outs will be evaluated to assess their comparability to either a) all others still on study (missing completely at random) or b) to others still on study within their site by study group (missing at random).

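### The ITT definition requires at least one dose, contradicting the analysis overview; if it governs, the primary months 0-9 immediate-versus-delayed comparison is no longer randomised

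*Protocol*

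**What the plan says.** Protocol section 10.4 (Methods of Analysis) defines the ITT population as those who are "randomized into the study and receive at least one dose of study medication". It defends leaving out undosed men on the ground that "the decision to not initiate study medication is made with no knowledge of the randomized treatment". The only other population in that section covers all screened men and serves descriptive summaries of study conduct.

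Section 10.1 (Study Design and Analysis Plan Overview) states a different rule under the same intent-to-treat name: "all data from enrolled participants will be analyzed according to the initial randomization assignment regardless of how many doses they received".

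The timing of the first dose differs by design. For the immediate arms, "Study product must be initiated within 24 hours after the enrollment visit" (Enrollment Visit). For the delayed arms, "Participants randomized the delayed treatment arms will receive study product at 9, 10 and 12 months" (Study Product Handling and Packaging). The Randomization section says that the envelope gives staff the participant's "assignment to a delayed or immediate arm and the randomization number".

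Behavioral safety is one of the two primary endpoints (10.2.1). Its main analysis (10.6) will "compare the overall level of selected behaviors in the immediate and delayed treatment arms over the first nine months".

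**The concern.** An at-least-one-dose rule is often harmless where everyone is offered product at randomisation under blinding. Here one side of a primary comparison cannot meet it until the comparison period is ending. An immediate-arm man lost at month 4 has been dosed and counts. A delayed-arm man lost at month 4 has not been dosed and does not count.

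The delayed group would therefore be selected on staying in the study, remaining without confirmed infection, and choosing to start at month 9. All of these arise after randomisation. Men who leave early or become infected may well differ in risk behavior, which is the outcome under study. A spurious difference in one direction would look like behavioral disinhibition, and in the other direction would hide it.

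The blinding argument does not help. It covers TDF versus placebo, but whether a man starts now or in nine months is known to him and to the staff.

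Because the protocol also states the opposite rule, an analyst could defend either population after seeing the data.

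**Working it through.** **1. The plan's own power figure.** Section 10.6 claims more than 80% power for a 12-point difference with a delayed-group rate of at least 28%. Inputs: 28% versus 40%; 200 per group (400 men in four equal arms); three post-baseline assessments (months 3, 6, 9); two-sided alpha 0.05; within-person correlation 0.5. The protocol gives that alpha for the SAE power and that correlation for adherence, so both are assumptions here, as is two-sidedness.

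- Effective n = n × T / (1 + (T − 1) × rho) = 200 × 3 / (1 + 2 × 0.5) = 300 per group; power 87.5%.
- With correlation 0.3 power is 93.6%; with 0.7 it is 81.0%.
- A single time point gives 71.8%.

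The stated figure is reproduced with repeated measures and all 200 men per group.

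**2. How many delayed-arm men the dosing rule would remove.**

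- Loss: section 10.3 expects 10-20% over 24 months. Spread evenly, the nine-month share is 10% × 9/24 = 3.75% to 20% × 9/24 = 7.5%, or 7.5 to 15 of 200. A constant hazard raises the upper value to 200 × (1 − 0.80^(9/24)) ≈ 16.
- Infection: the Target Populations section gives 2.8% without a time unit. Read as annual, 200 × 0.75 × 0.028 = 4.2 men. If it were cumulative over 24 months, 200 × 0.028 × 9/24 = 2.1.
- Total on the annual reading: about 12 to 20 of 200 (6-10%), against about none of the immediate-arm men.

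**3. Effect on power.** With 180-188 delayed-arm men against 200, power is 85.7-86.5% instead of 87.5%. Power is not the problem.

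**4. Illustrative bias.** Suppose there is no true difference and a prevalence of 28%. Let e be the share of delayed-arm men removed and q the prevalence at their assessments. With even loss, a third leave before month 3, a third between months 3 and 6, and a third between months 6 and 9. They supply 0, 1 and 2 of the three assessments, on average 1 of 3. Their share of delayed-arm assessments is

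w = (e/3) / (1 − 2e/3),

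and the false difference (immediate minus delayed) is w × (q − 0.28) / (1 − w). The values of q are assumptions; the protocol gives none.

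| e | w | q = 45% | q = 60% | q = 10% |
|---|---|---|---|---|
| 6% | 2.1% | +0.4 | +0.7 | −0.4 |
| 8% | 2.8% | +0.5 | +0.9 | −0.5 |
| 10% | 3.6% | +0.6 | +1.2 | −0.7 |

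All entries in the last three columns are percentage points.

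**5. HIV incidence.** Most of the roughly 4 delayed-arm infections expected in months 0-9 would also leave the count, while immediate-arm infections in the same months would stay.

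**The case against.** The strongest reply is that the exclusion is not certain. Section 10.1 keeps everyone, zero doses included. Section 10.6 names no dosed-only set and plans to compare drop-outs with men still on study, which presupposes that drop-outs are in the data. The Study Design section describes the delayed arms as the no-pill group for this very comparison. All of that stands, and it makes this a contradiction to be resolved rather than an established exclusion. It does not make the text safe: 10.4 is the passage that formally defines the population, and it argues expressly for leaving out undosed men.

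A reader might also infer more than the documents support:

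- *Every delayed-arm man infected before month 9 is lost, so the count is zero by construction.* Too strong. Product at month 9 follows a rapid antibody test, so a man infected shortly before and still antibody-negative could be dosed and included.
- *The bias is 1.5 to 2.8 points.* That follows at e = 8% only if each removed man is given full weight: 0.08 × (0.45 − 0.28) / 0.92 = 1.5 and 0.08 × (0.60 − 0.28) / 0.92 = 2.8. Men who leave before month 9 have not supplied all three assessments. An interview at the early termination visit would raise their weight, but not to full for those lost without one.
- *HIV incidence is seriously distorted.* It is a secondary, descriptive endpoint. The protocol expects few infections and plans qualitative case descriptions for infected men.
- *A broader population recovers all the data.* It recovers only what was collected before exit. Men lost to follow-up supply nothing later, and the Part B visits list no behavioral interview.

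**Conclusion.** The point holds as a contradiction between 10.1 and 10.4 with a specific consequence. If the dosing rule governs, a primary comparison is conditioned on post-randomisation retention on one side only, and the reason given for the exclusion does not apply to the disclosed immediate/delayed assignment.

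The bias is modest on the figures available and its direction is unknown. It rests on even accrual of loss, an annual reading of the 2.8%, assumed prevalences among the removed men, and an average of one assessment in three from each. Extra early-termination interviews would raise it somewhat. The case for correction does not depend on that size: a primary randomised comparison should not depend on which of two incompatible definitions is followed, and one of them breaks the randomisation.

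**What to change.** Reconcile sections 10.1 and 10.4:

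- Define ITT as all randomised men, excluding at most those found ineligible on pre-randomisation data (10.4 already allows this exclusion).
- Use that population for every immediate-versus-delayed analysis and for HIV incidence, with time counted from randomisation and all data up to exit included.
- Rename the at-least-one-dose set as a modified ITT or safety population. Limit it, and the sentence justifying it, to TDF-versus-placebo comparisons, where assignment is blinded.
- State in 10.6 which population the months 0-9 comparison uses.

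The cost is wording only. No visit or assessment is added, because scheduled evaluations already cover participants whether or not they take product.

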## Sample Size and Power Calculations

Recruitment will target 400 healthy, HIV-uninfected MSM that will be equally distributed across four treatment arms. Based on previous HIV prevention studies of similar length among MSM, it is estimated there will be an approximately 10-20% loss to follow-up over the study period.

Within the constraint of four study arms (TDF vs. placebo by immediate vs. delayed) and a total

study size of 400 participants, two design issues were explored: allocation of participants to the

four study arms and amount of time needed before the delayed arms began receipt of study

product. These evaluations were focused on the need to achieve a balance between good statistical properties (i.e., power) for the evaluation of both clinical AEs and behavioral outcomes as well as satisfy other criteria such as maximizing participation, especially in the delayed arms.

Equal allocation of participants to each study arm was found to be the best overall allocation scheme given the goals of the study. Additionally, a nine-month lead-in period for the delayed arm provided the best compromise between concerns for statistical power for comparisons of behavioral outcomes and logistical problems related to recruitment.

Sample size calculations for safety are expressed in the terms of the ability to detect SAEs. The following tables show the probabilities of observing, 0, 1, 2, 5+,  8+ or 10 or more SAEs among groups of n=100 (the immediate arm) and n=200 (both arms) for a range of possible true event rates. For example, if the true SAE rate is 3%, the probability of observing five or more events is 18.2% with n=100 and 71.9% with n=200.

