Three types of safety analyses will be performed depending on the outcome of interest as described in the next three sections. All safety analyses described will be adjusted for study site and the delayed /immediate treatment group variable. It will be explored whether these factors modify (i.e., effect modifiers) any of the observed outcome – treatment relationships and whether study drop-outs are comparable to either a) all others still on study (missing completely at random) or b) to others still on study within their site by study group (missing at random).

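### Section 10.3 bases SAE power on an exact or likelihood ratio test as if they were equivalent; only the two-sided Fisher exact test gives the table, and the analysis sections name no exact test.

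*Protocol*

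**What the plan says.** Section 10.3 expresses the safety sample size in terms of SAEs. On power it says "Power is calculated based on the exact test (or likelihood ratio test", followed by "The type 1 error is assumed to be 0.05"; it does not give sidedness. The comparison is made "given SAE rate in placebo group equals 0.01", in a table headed "SAE Rates in Treatment Group (n=200", with power of 17, 36, 56, 73 and 85% for TDF rates of 3, 4, 5, 6 and 7%. The confidence intervals in the same section are Blyth-Still-Casella, which are exact.

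Section 10.4 classifies outcomes by type: Cox regression for time to a first event, logistic regression for one yes/no response, and longitudinal, Poisson or linear models otherwise. All analyses are to run in PROC PHREG or "PROC GENMOD (logistic, Poisson, linear regressions for single or multiple responses". Section 10.5 adds that "All safety analyses described will be adjusted for study site and the delayed /immediate treatment group variable". It gives SAEs a separate tabulation and names no test for them. No exact test appears in Sections 10.4 or 10.5, and neither section chooses between Wald and likelihood ratio inference.

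**The concern.** Two statements do not fit together. First, Section 10.3 offers two tests as if either could stand behind the table. With about two expected placebo events (200 × 0.01), the two tests behave very differently. Second, the test that does give the table appears nowhere in the analysis methods, which list large-sample regression models only.

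At stake is whether the SAE comparison would have the power and error rate that Section 10.3 states. The tables that matter most are those with several SAEs on TDF and none on placebo. The odds ratio is then infinite, and large-sample methods are least reliable.

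**Working it through.** **Inputs.** The placebo rate of 1%, the TDF rates of 3 to 7%, alpha 0.05 and n = 200 on TDF come from Section 10.3. The 200 on placebo follow from "Recruitment will target 400 healthy, HIV-uninfected MSM that will be equally distributed across four treatment arms". The section expects "approximately 10-20% loss to follow-up over the study period", but the table makes no allowance for it, so none is made here.

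**Method.** Let x and y be the SAE counts on TDF and placebo. Power = Σx Σy Bin(x; 200, p1) × Bin(y; 200, p0) × 1[p-value(x, y) ≤ 0.05], summed over all outcomes. The three p-values are:
- two-sided Fisher exact;
- likelihood ratio: G = 2[ℓ(x/200) + ℓ(y/200) − ℓ(pooled)] against chi-square on 1 df, where ℓ is the binomial log-likelihood;
- Wald from an unadjusted logistic model: z = ln(OR) / √(1/x + 1/(200−x) + 1/y + 1/(200−y)). With x = 0 or y = 0 it is undefined and counted as not significant.

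**Results, placebo rate 1%.**

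| TDF rate | Protocol | Fisher, two-sided | Likelihood ratio | Wald |
|---|---|---|---|---|
| 3% | 17% | 16.9% | 36.3% | 9.9% |
| 4% | 36% | 36.0% | 56.5% | 26.5% |
| 5% | 56% | 56.3% | 73.6% | 46.1% |
| 6% | 73% | 73.5% | 85.5% | 62.8% |
| 7% | 85% | 85.5% | 92.8% | 74.2% |
| 1% (type I error) | 5% nominal | 0.5% | 9.6% | 0.1% |

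The two-sided Fisher column reproduces the protocol's table. One-sided Fisher (26.0/48.2/68.5/83.1/91.8%) and Pearson chi-square (27.8/48.9/68.5/82.7/91.4%) do not. The likelihood ratio test lies 7 to 20 points above Fisher.

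**Adjusted model.** A simulation of the logistic model adjusted for site and immediate/delayed group (20,000 replicates, three equal sites assumed) gives Wald power of about 11/28/49/64/75%. That is 6 to 10 points below the table. The likelihood ratio type I error stays at 9.6%.

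**Source of the differences.** The chance of no placebo SAE is 0.99^200 = 13.4%.
- At 3 v 0, G = 2[3 ln(3/200) + 197 ln(197/200) − 3 ln(3/400) − 397 ln(397/400)] = 4.18, p = 0.041. Fisher gives 2 × (200·199·198)/(400·399·398) = 0.25 and first rejects at 6 v 0.
- Wald cannot reject at any count against zero, including 14 v 0, where Fisher p = 0.0001.
- With 1, 2, 3 or 4 placebo events, the smallest TDF count that rejects is 8, 10, 11, 13 for Wald and 8, 10, 12, 13 for Fisher.
- At a 6% TDF rate, given at least one placebo event, power is 72.5% for Wald and 69.6% for Fisher. Weighted by 0.866, these contribute 62.8% and 60.3%. Fisher gains its other 13.2 points (73.5 − 60.3) from trials with no placebo SAE; Wald gains none there.

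**Higher rates.** At 2% v 7%, Wald power is 63.2% against 60.9% for Fisher. With 5% in both groups, type I error is 5.5% for the likelihood ratio test and 3.8% for Wald.

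**The case against.** A reader might infer that the protocol plans to test SAEs by logistic regression, so that the SAE comparison is bound to miss its stated power and error rate. The documents do not support that. Section 10.5 only tabulates SAEs. The list in Section 10.4 is generic and also offers Cox regression. A procedure is named but no test statistic, and that choice is commonly left to a statistical analysis plan, which is not shown. The Wald loss and the likelihood ratio inflation are therefore consequences of two options, neither of which has been selected.

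It is also true that the Wald deficit comes wholly from trials with no placebo SAE, and that both effects fade as rates rise. The Fisher test misses the nominal 5% too: its actual size at 1% is 0.5%, a real cost when the aim is to detect harm.

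These objections narrow the point but do not remove it. The sentence in Section 10.3 is incorrect however SAEs are tested. Section 10.3 powers a between-group SAE comparison, while Section 10.4 confines all analyses to two regression procedures. If no comparison is intended, the power table describes an analysis that will not be done, and the sections still need reconciling. The Cox route is not an exact test either.

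**Conclusion.** The point holds in a limited form. Section 10.3 is wrong to present the exact and likelihood ratio tests as alternatives: only the two-sided Fisher test gives its table. The analysis sections contain no exact test that would deliver the stated power.

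If the general rule for yes/no outcomes is applied to SAEs at a 1% placebo rate, power is 7 to 11 points below the table with a Wald test (6 to 10 when adjusted, assuming three equal sites). With a likelihood ratio test the error is about 9.6% instead of 5%. These figures assume 200 per group with no losses, as the table does.

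A reader might also extend this to the main clinical safety outcome. The synopsis defines that as the proportion with grade 3 or 4 abnormalities, and the Introduction reports 29% for the TDF group of study 903. Those were HIV-infected patients, so the figure is only a guide. At rates anywhere near it, logistic regression is suitable and the concern does not apply.

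**What to change.** In Sections 10.4 and 10.5, state that SAEs and other adverse event types with few events are compared by an exact test with an exact confidence interval, and keep logistic regression for common outcomes such as any grade 3 or 4 event. The exact test may be stratified by site and immediate/delayed group, with a note that power may then differ slightly from the unstratified table. In Section 10.3, remove the likelihood ratio alternative and state that the table is for a two-sided Fisher exact test at 0.05.

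The cost is about one sentence in each place and a different procedure call. The drawback is that the exact test is very conservative at 1% (actual size about 0.5%), but the stated power already reflects this.
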